### Data collection and management

All data will be directly entered on REDCap, or recorded on case report forms (CRFs) and stored anonymously in a locked cabinet at the Exercise Oncology Research Laboratory, at the University of Alberta before, during, and after the trial. The investigators will provide access to the data file on reasonable request. The investigator is ultimately responsible for the collection and timely reporting of all applicable data entered in CRFs and ensuring they are accurate, original, attributable, complete, legible, contemporaneous, and available when required. A Data Monitoring Committee will not be involved in this study as it is a short-term in its duration, in its early stages, and based on the intervention and outcome of interest, the potential for harm to study participants is deemed to be minimal, if any. De-identified research data will be made publicly available when the study is completed and published.

### Statistical considerations

All randomized participants will be included in the analysis using an intention-to-treat approach. There will be no interim analyses. If missing data is < 10% we will conduct a complete case analysis. If missing data is > 10%, we will employ a multiple imputation missing data strategy [54,55]. Continuous variables will be described using mean (standard deviation) or median (interquartile range). Categorical variables will be described using frequencies (percentages) and confidence intervals. Descriptive analyses will be performed for participant characteristics, feasibility outcomes, adherence, and adverse events. Analysis of covariance will be performed to compare post-intervention between-group differences post-intervention in health-related fitness and patient-reported outcomes for patients with evaluable data. We will adjust for covariates such as baseline physical function levels, cancer stage, HPV status, treatments received (surgery, chemotherapy/radiotherapy, surgery + chemoradiotherapy), and time since treatment completion in the primary analysis. IBM SPSS Statistics version 28 will be used for all statistical analyses. The level of statistical significance will be set at 0.05, and all hypotheses’ tests will be two-sided.

Strategies to minimize dropouts and protocol deviations include: 1) a progression period of at least 5-weeks is in place to reach heavy loads (80% to 100% of maximal perceived exertion) in the barbell squat, bench press, and deadlift; 2) reducing the load, number of sets, and/or repetitions; 3) allowing for multiple rest days in between the two weekly exercise sessions; and 4) participants in the Usual Care Group will be offered a 4-week introduction to HLST program and/or referred to a community-based exercise program to encourage their adherence to the protocol, and to thank them for their time in the study. All participants who withdraw from the study will be invited to complete the follow-up assessments to avoid missing data for the intention-to-treat analyses.

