### Recruitment and screening

Potentially eligible participants will be identified and contacted via the Alberta Cancer Registry, a database that holds information pertaining to all living and deceased individuals diagnosed with cancer in the province of Alberta, Canada. By recruiting in this way, we will have contacted all potentially eligible HNCS at least one-year post-treatment.

Interested HNCS will contact and meet with the study coordinator ([name]) via an online pre-screening meeting, which will serve as a chance to ask about medical history such as type of cancer, cancer stage, and treatment type, elaborate further on study details, and obtain verbal informed consent at this time. Once online questionnaires are complete in the Research Electronic Data Capture (REDCap), and the study coordinator will schedule interested HNCS for in-person baseline physical assessments at the Exercise Oncology Research Laboratory at the University of Alberta. Finally, eligibility will be determined through objective measurements of active shoulder flexion and abduction ranges of motion. To satisfy eligibility criteria #2 above, participants will be required to meet or exceed the following age-based cut points for shoulder range of motion: participants 18–50 years old: ≥ 150° for flexion and abduction; participants over 50 years old: ≥ 130° for flexion and abduction.

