#### Demographic variables.

Demographic variables will be assessed using self-report. Medical data will be obtained via self-report by the participants, and include: type of HNC, type of treatment modality and dissection type, cancer recurrences if any, comorbidities, current and previous injuries, and a list of medications.

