The LIFTING 2 trial has several limitations including its modest sample size, the absence of long-term follow-up, and the absence of a correlative (biological) component such as gene expression alternations that may be associated with HNC recurrence. This single-centre study is primarily aimed at further establishing the feasibility of HLST, and is underpowered to determine the efficacy of exercise on clinical outcomes of cancer recurrence. In the future, we plan to scale this intervention to include multiple centres. If this current LIFTING 2 study establishes feasibility, safety, and efficacy, we can then estimate how many sites would be needed to properly power a phase III trial. A multi-site study would then allow for a greater sample size, as well as greater validity and generalizability of our study findings. Potential barriers to implementation that may take place in a future multi-site study may include: variations in procedures and practices between sites, communication breakdown and challenges across different time zones, standardization in exercise delivery methods may be challenging with various levels of experience, and possible differences in protocol training conducted for exercise supervisors at each site. The recurrence rate of all HNC subtypes is approximately 50% but may vary depending on cancer stage and HPV status [72]. We will follow-up on health-related fitness and patient-reported outcomes at post-intervention (12-weeks) to determine the direction and magnitude of short-term changes between the groups. We will not follow-up on any long-term cancer outcomes. We will also determine if there are any meaningful changes in the hypothesized direction, although we acknowledge that there is a low likelihood of demonstrating a statistically significant effect. Minimal clinical important differences in upper and lower body muscular strength changes are not clearly reported in the literature, however, standardized effects sizes of 0.50 standard deviations are widely considered clinically important. Other minimally important changes include: 5.0–6.5 kg for handgrip strength [73]; ≥ 2 repetitions for the 30 second sit to stand test [74]; 14.0–30.5 metres in the 6-minute walk test [75]; 2–10° in active shoulder flexion or abduction [76,77]; 5–10 points for quality of life [78]; 6 points for insomnia [79]; and a ≥ 5% weight loss in one-month or ≥10% weight loss in six-months for malnutrition risk assessment [51]. This information will aid in the development of research objectives and the design of larger exercise studies in HNCS.

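### The analysis paragraph promises all randomised participants under intention-to-treat but runs the efficacy ANCOVA on evaluable patients, with a missing-data switch at an undefined 10%

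*Protocol article*

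**What the plan says.** Everything at issue in the analysis stands in one paragraph of the protocol article, under Statistical considerations:

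- Population: "All randomized participants will be included in the analysis using an intention-to-treat approach".
- Low missingness: "If missing data is < 10% we will conduct a complete case analysis".
- Higher missingness: "If missing data is > 10%, we will employ a multiple imputation missing data strategy".
- Efficacy comparison: an ANCOVA of "health-related fitness and patient-reported outcomes for patients with evaluable data". This restriction is not tied to either missing-data branch.
- Model: "We will adjust for covariates such as baseline physical function levels, cancer stage, HPV status, treatments received", followed by time since treatment completion, in the primary analysis.

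The paragraph also says that participants who withdraw will be invited to the follow-up assessments.

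On data collection, the section Demographic variables says that medical data are self-reported and gives this list: "type of HNC, type of treatment modality and dissection type, cancer recurrences if any, comorbidities, current and previous injuries, and a list of medications". Recruitment and screening says the pre-screening meeting covers "medical history such as type of cancer, cancer stage, and treatment type". Table 3 has one general row for self-reported medical information at baseline. Apart from the covariate list, HPV status is mentioned only as background in the Discussion, where recurrence "may vary depending on cancer stage and HPV status".

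**The concern.** A complete-case analysis, or one limited to evaluable patients, excludes randomised participants by construction. The opening sentence of the paragraph says nobody is excluded. An analyst must therefore break one of the rules, and the text does not say which takes precedence.

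Three consequences follow.

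- **Label.** A result from evaluable patients could be reported as intention-to-treat.
- **Covariates.** ANCOVA software drops any record with a missing covariate. A participant with baseline and 12-week 3RM values but no recorded HPV status would be lost although the primary efficacy outcome was measured.
- **Switch.** The 10% has no denominator (participants, outcomes or data values), and exactly 10% falls in neither branch. The same data set could be sent to either method. Participants, investigators and outcome assessors all know the allocation, so this choice is better closed in advance.

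**Working it through.** **1. The plan's own sample size.** Inputs from Sample size: standardised effect d = 0.80, R² = 0.25, two-sided alpha 0.05, power 0.80, loss 20%.

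n per arm = 2(1 − R²)(1.960 + 0.842)² / d² = 2 × 0.75 × 7.849 / 0.64 = 18.4, rounded up to 19, so 38 evaluable. Then 38 / 0.80 = 47.5, rounded up to 48. Both stated figures reproduce, and the sample size is not in question.

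**2. Which branch applies, counting participants.** With 48 randomised:

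- 4 missing: 4/48 = 8.3%, complete case, leaving 44.
- 5 missing: 5/48 = 10.4%, multiple imputation.
- The allowed 20% loss, 48 − 38 = 10: 10/48 = 20.8%, multiple imputation.

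On this reading the complete-case branch drops at most 4 people. Power at N = 44 is about 0.85 (noncentral t) to 0.865 (normal), above the planned 80%.

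**3. Which branch applies, counting data values.** Take seven model variables: outcome, arm, baseline, stage, HPV status, treatment and time since treatment. There are 48 × 7 = 336 values.

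- Ten missing outcomes alone: 10/336 = 3.0%, complete case.
- Ten missing outcomes plus 8 unknown HPV values (assumed, all among those with outcomes): 18/336 = 5.4%, still complete case. This analyses 48 − 18 = 30, although 38 have a measured outcome.

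The same 10 lost outcomes thus lead to imputation under one reading and to complete-case analysis under the other.

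**4. Size, as illustration only.** Assume the evaluable restriction overrides imputation and that 4 or 8 of the 38 are also dropped for a missing covariate (roughly 10% or 20%). The documents give no such rate. Power is from the noncentral t distribution, with noncentrality d / √(1 − R²) × √(n/2), n = N/2, and N − 2 − k degrees of freedom for k covariate degrees of freedom (k is also an assumption).

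| N analysed | Noncentrality | Power, k = 7 | Power, k = 1 |
|---|---|---|---|
| 38 | 0.9238 × √9.5 = 2.85 | 0.786 | 0.791 |
| 34 | 0.9238 × √8.5 = 2.69 | 0.735 | 0.742 |
| 30 | 0.9238 × √7.5 = 2.53 | 0.675 | 0.684 |

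**5. Is HPV status listed for collection?** It is absent from the medical data list, the pre-screening items and Table 3. But the medical data list also omits cancer stage and time since treatment. Stage is asked at pre-screening and used for stratification, and time since treatment decides eligibility. That list is therefore not complete.

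**The case against.** The strongest reply is that the paragraph holds a two-branch rule and should be read as a whole: complete cases when little is missing, imputation otherwise. On a per-participant count the allowed 20% loss goes to imputation, so little is lost. Withdrawn participants are invited back for assessment, the trigger is a prespecified fraction rather than a result, and efficacy is a secondary, preliminary aim. Much of this stands. It does not remove the contradiction, because the evaluable restriction on the ANCOVA is unconditional and because even the low-missingness branch excludes people the first sentence includes.

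Three stronger readings may tempt a reader, and the documents support none of them.

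- **That complete-case analysis is the general plan.** The same paragraph prescribes imputation above 10%.
- **That HPV status will not be collected.** The lists use open wording, the medical data list is demonstrably incomplete, and the article condenses a fuller protocol. The fair statement is that no source is shown.
- **That deleting people with unknown HPV status breaks the randomised balance.** Medical information is taken at baseline, before allocation, so its absence is unrelated to arm in expectation. Deletion costs precision; it does not of itself bias the comparison. Missing 12-week outcomes differ, since they arise after randomisation, but nothing in the document allows that effect to be sized.

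**Conclusion.** The point holds as an internal inconsistency. The analysis population is stated in incompatible ways, and the rule for choosing the method has no denominator. (Exactly 10% is a lesser gap: 10% of 48 is 4.8, so it cannot occur on a participant count at full recruitment.) As written, randomised participants can be left out of an analysis called intention-to-treat, including some with both 3RM tests done.

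The size is uncertain. If missingness is low and counted by participant, at most 4 of 48 are lost and power stays above target. The fall from about 0.79 to between 0.74 and 0.68 needs two assumptions that the document does not settle: that the evaluable restriction overrides imputation, and that 4 to 8 of the 38 lack a covariate. It shows scale and is not a forecast. The wording should be corrected before analysis; design and recruitment target are unaffected.

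**What to change.** In Statistical considerations:

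1. Delete the restriction to evaluable patients and the 10% switch.
2. Make one all-randomised analysis primary whatever the missing fraction: either multiple imputation with arm, baseline 3RM, sex and stage in the imputation model, or a mixed model of baseline and 12-week 3RM. Keep complete cases as a sensitivity analysis.
3. State that missing baseline covariates are imputed or coded as unknown, so that no participant with a measured outcome is dropped. This is needed with the mixed model too, which would otherwise lose the same records.
4. Name the source of HPV status, or use it only in a sensitivity analysis. Either is acceptable, and taking it from clinical records is optional.

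Imputing an absent 12-week 3RM will add little precision by itself. The gains are an analysis that matches its label and the retention of people whose outcome was measured. The cost is protocol wording and a little more analysis work, plus a record extract only if the investigators choose that source for HPV status.

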Here, we propose the Feasibility and Preliminary Efficacy of Heavy Lifting Strength Training versus Usual Care in Head and Neck Cancer Survivors (the LIFTING 2) trial, the first phase II, randomized controlled trial that will further establish the feasibility of HLST using free weights, and provide preliminary efficacy data compared to Usual Care (UC) in HNCS. The primary efficacy outcome is upper and lower body muscular strength changes from baseline to post-intervention, assessed by reliable 3 repetition maximum (3RM) tests. Secondary efficacy outcomes include physical function, shoulder mobility, and handgrip strength assessed by validated physical assessments; body composition components such as skeletal muscle mass and body fat percentage assessed by bioelectrical impedance; and quality of life (QoL), fear of cancer recurrence, symptom burden, fatigue, self-esteem, sleep, swallowing abilities, and nutritional status assessed by well-validated questionnaires. We hypothesize that HLST will be safe and feasible for HNCS, and anticipate no adverse events to occur which are directly related to HLST [28–30]. Lasty, we expect that HLST will be superior to UC for muscle strength, mass, and function, and QoL.

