#### Health-related fitness outcomes.

3RM assessments will be used to assess upper and lower body strength with the leg press and chest press machines. RIR will be used to assess the perceived intensity of these exercises and this may be the optimal way to assess exercise intensity in terms of safety, reliability, validity, and tolerability [31]. The 3RM test is reliable and the gold standard assessment to evaluate maximal strength of resistance exercises in ‘healthy’ men and women, and it can be used by athletic trainers, health and fitness professionals and rehabilitation specialists to quantify the level of strength, to assess strength imbalances, and to evaluate training programs [31,35]. 3RM, RIR, and RPE scales are equally effective at improving muscular strength and functional performance in an older population [31], and we expect the majority of participants to be of middle to older age due to the typical age of onset of HNC.

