#### Physical function.

Physical function assessments for participants 50 years old and up will include: 6 Minute Walk Test (6MWT), and 30 second sit to stand to assess aerobic functional capacity and lower body muscular endurance [42,43]. Active shoulder flexion and abduction ranges of motion will be measured using a goniometer to ensure ranges meet the cut points required for study eligibility outlined above. Handgrip strength will be assessed using a handgrip dynamometer [44].

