### Sample size

Our goal will be to recruit 48 HNCS. With 80% power, a two-tailed alpha of p < 0.05, and adjusting for covariates that explain 25% of the variance in the outcome, we will be able to detect a standardized effect size 0.80 with 38 (19/group) evaluable HNCS allowing for a 20% loss to follow-up. We believe that this large effect on strength is realistic in our study, given that we are comparing HLST to no exercise. Additionally, all participants would not have participated in any sort of strength training within at least the past one-month. As it is difficult to power a feasibility trial on the feasibility outcomes, we have powered the trial on the first indicator of efficacy, which is muscular strength. Our study is approaching all HNCS in the Edmonton and surrounding area. Therefore, there is no viable secondary plan if the target accrual is not reached. Based on an initial review by the Alberta Cancer Registry, there are approximately 1,495 HNCS living in the Edmonton area. Based on our previous studies [13,14,20–22,25,28,52,53], we expect around 50% to be eligible and a recruitment rate of about 6%, which will allow us to reach our target.

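### The ANCOVA on post-intervention 3RM does not name baseline 3RM as a covariate, so precision that costs nothing may be lost

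*Protocol article*

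**What the plan says.** The Introduction defines the primary endpoint as a change: "The primary efficacy outcome is upper and lower body muscular strength changes from baseline to post-intervention", measured by 3RM. Maximal strength testing schedules the leg-press and chest-press 3RM at baseline and again after the intervention.

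Statistical considerations plans an ANCOVA comparing post-intervention values between groups. For the primary analysis it states: "We will adjust for covariates such as baseline physical function levels, cancer stage, HPV status, treatments received", followed by time since treatment completion. Neither baseline 3RM nor, more generally, the baseline value of the analysed outcome is mentioned.

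Table 3 lists the 3RM tests under health-related fitness, and the matching text agrees: "3RM assessments will be used to assess upper and lower body strength with the leg press and chest press machines". Physical function has its own heading in Table 3, covering the 6-minute walk, sit-to-stand, shoulder range of motion and handgrip. Its text begins: "Physical function assessments for participants 50 years old and up will include: 6 Minute Walk Test (6MWT), and 30 second sit to stand". Eligibility starts at 18 years.

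The sample size rests on "adjusting for covariates that explain 25% of the variance in the outcome", without saying which covariates supply that 25%.

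**The concern.** In an ANCOVA of a post-intervention measurement, the covariate that usually matters most is the same measurement at baseline. Post-intervention 3RM is an absolute load, so much of its spread will be stable differences between people. Baseline 3RM is the direct measure of those differences, and the trial already collects it.

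An analyst who follows the sentence literally would adjust for a walk test, a chair-stand count, a shoulder angle or a grip reading instead. Sex, a stratification factor and a plausible predictor of load lifted, is not in the list either. The residual variance would then be larger than necessary, and a chance difference in starting strength between two groups of about 19 could go largely uncorrected.

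A second difficulty arises if the covariate chosen is the 6-minute walk or sit-to-stand: participants under 50 have no scheduled value for it.

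**Working it through.** **Inputs.** From Sample size: two-sided alpha 0.05, power 80%, standardised effect d = 0.80, covariate R² = 0.25, 19 evaluable per group, 20% loss, 48 recruited. Assumed, because the document does not give it: a baseline-to-post 3RM correlation r of 0.6 to 0.9, with R² = r².

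**Reproducing the plan's figure.** Normal formula: n per group = 2 × (1.960 + 0.842)² × (1 − 0.25) / 0.80² = 18.4, rounded up to 19, so 38 evaluable. Allowing for loss: 38 / 0.80 = 47.5, rounded up to 48. Both stated figures are correct. Power at 19 per group is 81% by the normal formula and 79% by the noncentral t.

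**Effect of naming baseline 3RM.** Noncentral t with noncentrality d / √(1 − R²) × √(19/2) and df = 38 − 2 − 1 = 35. At 80% power the detectable effect is about 0.935 × √(1 − R²), where 0.935 SD is the value at R² = 0. The 95% CI half-width in SD units is t(0.975, 35) × √(1 − R²) × √(2/19).

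| Model | R² | Detectable effect (SD) | Power at 0.80 SD | CI half-width (SD) |
|---|---|---|---|---|
| As planned | 0.25 | 0.81 | 79% | 0.57 |
| r = 0.6 | 0.36 | 0.75 | 85% | 0.53 |
| r = 0.7 | 0.49 | 0.67 | 92% | 0.47 |
| r = 0.8 | 0.64 | 0.56 | 98% | 0.40 |
| r = 0.9 | 0.81 | 0.41 | >99% | 0.29 |

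At r = 0.5, R² is 0.25 and there is no gain over the planning assumption.

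**Sensitivity to the number of covariates.** A model with the baseline value (1 df), sex (1), stage in two levels (1), HPV status (1), treatment in three categories (2) and time since treatment (1) uses 7 df. The detectable effects are then 0.81, 0.75, 0.67, 0.56 and 0.41 SD, unchanged to two decimals. At 0.50 SD, which the Discussion calls widely accepted as clinically important, power is 41% at R² = 0.25 and 46%, 55%, 70% and 93% at r = 0.6, 0.7, 0.8 and 0.9.

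**If the named covariates explain less than planned.** At R² = 0.10, power at 0.80 SD is 72% (noncentral t, one covariate); at R² = 0 it is 67%.

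**The age-restricted tests.** Complete-case analysis applies below 10% missing. If the covariate were the walk test or sit-to-stand, and 5% or 10% of the 38 were under 50 (share assumed), about 36 or 34 would remain. Power at R² = 0.25 would then be 77% or 74% by the noncentral t. Above 10%, multiple imputation would fill in values never scheduled for that age group.

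**The case against.** The covariate list is introduced as examples, so baseline 3RM is unnamed rather than excluded. A reader might infer that the model omits it, but the text does not go that far. The article's labels are also loose. The Abstract puts health-related fitness among the secondary outcomes although Table 3 uses that heading only for 3RM, so physical function might informally include strength. This stands as a reason to call the wording ambiguous. It does not remove the need to settle it: in a trial whose assessors and investigators are unblinded, the choice of baseline covariate should not stay open.

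A reader might also infer that an analysis without baseline 3RM is biased, or does not estimate change. Neither follows. Under randomisation the difference in post-intervention means and the difference in mean change have the same expectation; only precision and protection against chance imbalance are affected.

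Nor does the document show that participants under 50 will be lost. That requires the walk test or sit-to-stand to be the covariate and the complete-case rule to apply. Handgrip and shoulder range are not clearly age-restricted, and the article expects mostly middle-aged to older participants.

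Finally, the planned 25% may already include baseline 3RM. If so, the gain in the table is not attributable to the change. The efficacy comparison is also preliminary in a trial whose first aim is feasibility.

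**Conclusion.** The point holds as a gap in how the primary model is specified. The baseline value of the analysed outcome is not named, and the baseline measure that is named belongs, in the article's own table, to another outcome family with two tests limited to age 50 and over. The sample size is not wrong: 38 evaluable and 48 recruited both reproduce.

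What is at stake is precision: a detectable effect of about 0.81 SD, against 0.75 to 0.41 SD with baseline 3RM in the model. That range rests on two assumptions the document neither supports nor contradicts: a correlation of 0.6 to 0.9, and a planned R² of 0.25 that excludes baseline 3RM. The direction is clear for any correlation above 0.5; the size cannot be fixed from the document. This is a should-fix improvement, not a threat to validity.

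**What to change.** In Statistical considerations, replace baseline physical function levels with the baseline value of the outcome being analysed: baseline leg-press 3RM in the leg-press model, baseline chest-press 3RM in the chest-press model, and likewise for each secondary outcome. With that term included, analysing the post-intervention value or the change gives the same treatment effect, which also reconciles the ANCOVA with the Introduction's definition of the endpoint.

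Keep both stratification factors in the model. Stage is already listed; sex must be added. The list should not be closed before that, or it would shut out a stratification factor. Do not use the 6-minute walk or sit-to-stand as covariates in the primary model.

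The cost is one sentence of protocol wording. No new data, visits or participants are needed. The change should be made before outcome data are analysed.

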### Randomization and blinding

After completing baseline assessments, participants will be randomly assigned to either the HLST Group or the UC Group in a 1:1: ratio using a computer-generated program within REDCap, with random blocks of 4 or 6. The allocation sequence will be generated by and independent researcher and uploaded directly to REDCap to ensure concealment from study personnel. Participants will be stratified by biological sex and cancer stage (I-III vs. IV) to ensure balanced group distribution. Additional stratification variables will be considered in a future phase III trial. The UC Group was chosen as the comparator in order to evaluate the feasibility and efficacy of a HLST program. During the conception of this study, we considered comparing HLST to LMST but felt that we needed to further establish the feasibility of HLST before comparing it to LMST. A future phase III study would then compare HLST to LMST to determine the optimal exercise intensity for HNCS.

Group allocation will be shared with the participant immediately after the baseline assessment. Participants and investigators will not be blinded to group assignment, given the nature of the intervention. Outcome assessors will also not be blinded to group assignment because of logistical challenges. However, we will follow a standardized, detailed protocol and all assessors will be trained on the importance of standardizing outcome assessments and prioritizing safety.

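### Sex is a stratification factor but is not named among the primary ANCOVA covariates; if it is left out, the test is somewhat conservative and some power is forgone

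*Protocol article*

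**What the plan says.** Study design and Randomization and blinding in the protocol article both give two stratification factors. The latter states: "Participants will be stratified by biological sex and cancer stage (I-III vs. IV) to ensure balanced group distribution". Allocation is 1:1 in random blocks of 4 or 6.

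Statistical considerations specifies an analysis of covariance and names these terms for adjustment: "baseline physical function levels, cancer stage, HPV status, treatments received (surgery, chemotherapy/radiotherapy, surgery + chemoradiotherapy), and time since treatment completion in the primary analysis". The list is introduced by *such as*, so it is open. Sex is not named there, or anywhere else, as an analysis covariate.

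Table 3 puts 3RM leg press and chest press under muscular strength. The 6-minute walk, sit-to-stand, shoulder range and handgrip come under physical function. The Physical function section describes the walk and sit-to-stand tests as being for participants aged 50 and over.

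The Sample size section says "we have powered the trial on the first indicator of efficacy, which is muscular strength", assumes "adjusting for covariates that explain 25% of the variance in the outcome", and gives "we will be able to detect a standardized effect size 0.80 with 38 (19/group) evaluable HNCS allowing for a 20% loss to follow-up".

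**The concern.** Stratified blocking forces near-balance on sex, so sex contributes little to the true sampling variation of the treatment difference. An ANCOVA without sex does not know this. Whatever sex explains stays in the residual, and the reported standard error then exceeds the true one. Confidence intervals are too wide, the test rejects less often than its nominal 5% under the null, and power is below what a model with sex would give.

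This matters here because the primary efficacy outcome is an absolute load. Men and women can be expected to differ on it, and the investigators thought sex important enough to stratify on. The trial plans for only 38 evaluable participants, and the Sample size section says there is no fallback if accrual falls short, so precision cannot easily be recovered by recruiting more.

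**Working it through.** **Step 1: the plan's own figure.** Inputs from the Sample size section: "With 80% power, a two-tailed alpha of p < 0.05", effect 0.80 SD, covariate R² = 0.25, 20% loss.

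- Residual SD = √(1 − 0.25) = 0.866.
- n per group = 2 × (1.960 + 0.842)² × 0.75 / 0.80² = 18.4, so 19 per group and 38 evaluable.
- Recruitment = 38 / (1 − 0.20) = 47.5, so 48.
- Power at 19 per group: 81.3% (normal approximation) or 79.1% (noncentral t, 35 df).

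The stated figures reproduce.

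**Step 2: adding sex, by formula.** Let r be the partial R² of sex given the other covariates. The documents do not give r, so it is varied from 0 to 0.40. With sex in the model the residual SD becomes √(0.75 × (1 − r)). Power at 19 per group (normal approximation) is then 81.3% at r = 0, 83.2% at 0.05, 85.1% at 0.10, 88.9% at 0.20, 92.6% at 0.30 and 95.7% at 0.40.

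**Step 3: simulation of the stratified design.** There were 5,000 trials per setting, with 48 randomised in blocks of 4 or 6 within sex × stage and 38 evaluable at random. One baseline covariate explains 25% of the variance. Shares of 25% women and 50% stage IV are assumed, since neither is in the documents. The ANCOVA uses the baseline covariate and stage, without and then with sex. The SE, SD and type I error columns are under no effect; power is at 0.80 SD.

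| r | Model SE, sex omitted | True sampling SD | SE excess | Type I error, omitted | Type I error, included | Power, omitted | Power, included | Points forgone |
|---|---|---|---|---|---|---|---|---|
| 0 | 0.285 | 0.284 | 0% | 4.8% | 4.8% | 76.8% | 76.7% | 0 |
| 0.05 | 0.286 | 0.282 | 1% | 4.5% | 4.9% | 77.6% | 78.6% | 1 |
| 0.10 | 0.285 | 0.278 | 3% | 4.3% | 5.3% | 78.5% | 81.1% | 3 |
| 0.20 | 0.286 | 0.267 | 7% | 3.5% | 4.9% | 79.0% | 84.8% | 6 |
| 0.30 | 0.286 | 0.261 | 10% | 2.9% | 4.9% | 79.9% | 89.2% | 9 |
| 0.40 | 0.286 | 0.246 | 16% | 2.5% | 5.0% | 80.0% | 93.6% | 14 |

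The SE excess is model SE divided by true SD, minus 1. Points forgone are rounded differences of the two power columns.

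**Step 4: where r is likely to lie if baseline 3RM is in the model.** Suppose sex explains a share B of 3RM variance at both visits, W = 1 − B, and the within-sex correlation between visits is ρ. Then

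r = 1 − W(1 − ρ²) / [1 − (B + ρW)²].

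With B = 0.40 (an assumption), ρ = 0.9 gives 1 − 0.114/0.1164 = 0.02. Likewise ρ = 0.8 gives 0.04, ρ = 0.7 gives 0.07 and ρ = 0.5 gives 0.12. Baseline 3RM would therefore absorb most of the sex effect and place the trial in the upper rows of the table.

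**Step 5: the price of a degree of freedom.** At R² = 0.25 and 19 per group, going from 35 to 29 residual df lowers power from 79.1% to 78.6%. One df for sex costs about a tenth of a point.

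**The case against.** The strongest reply is that the covariate list is illustrative. Because it opens with *such as*, it does not exclude sex, and a condensed article may leave the final model to an analysis plan that is not shown. This stands to the extent that the protocol cannot be said to omit sex from the model. It can only be said to name one stratifier and not the other. An open list does not commit to sex either, and the article has chosen to say what the primary analysis adjusts for.

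The second reply is that the effect may be small. The Introduction describes the outcome as change in strength from baseline, and baseline 3RM is collected. If it enters the model, r falls to roughly 0.02 to 0.12 under the assumptions in Step 4. This also stands, but the text names baseline physical function rather than baseline strength, so it is not clear that baseline 3RM is included.

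A reader might go further and infer that the trial is underpowered or its sample size wrong. The documents do not support that: 19 per group and 48 in total reproduce, provided the covariates used explain the assumed 25%. The power forgone is measured against a model that includes sex, not against the plan's 80%.

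A reader might also take the ratio of the two models' standard errors, 1/√(1 − r), which is 12% at r = 0.20 and 29% at 0.40, as the overstatement. That ratio compares two models. The overstatement is model SE against true sampling SD: 7% and 16% at those values.

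**Conclusion.** The mismatch between the stratification factors and the named covariates is real, and its direction is certain if sex carries residual prognostic information. Omitting it makes the test conservative and gives up some power. The treatment estimate is unbiased and type I error is not inflated.

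The size is uncertain because the partial R² of sex is not in the documents. Over an assumed range of 0 to 0.40, the power forgone runs from nil to 14 points and type I error from about 4.8% down to 2.5%. The low end is likely if baseline 3RM is adjusted for. The higher values apply only if it is not and sex explains much of the remaining variance. The simulated model is simpler than the named list and assumes the shares of women and stage IV.

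Severity is minor to moderate, given that feasibility is the primary aim and efficacy is preliminary. Confidence is high for the mismatch and its direction, and moderate for its size.

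**What to change.** Before any outcome analysis, name the following as fixed covariates in the primary ANCOVA:

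- biological sex;
- cancer stage, in the grouping used for randomisation (I-III vs IV);
- the baseline value of the outcome being analysed, which is baseline 3RM leg press or chest press for the strength outcomes.

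For these terms, replace the open wording with a definite list. The change is a sentence in Statistical considerations. Sex costs one degree of freedom. No new data are needed, because sex is recorded for randomisation and 3RM is already measured at baseline. The sample size does not change.
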